### Procedures for data collection and management

#### Data collection

Basic and contact information (ID number, address and phone number), anthropometric data (waist circumference, height and weight), resting blood pressure, heart rate, ambulatory blood pressure, and information on socioeconomic status, risk factor control and current medications were collected at baseline at hospital recruitment sites. Detailed information on patient outcomes (hospitalisations, discharge diagnoses, etc) was also collected during the survey and hospital records or death certificates obtained where necessary for adjudication. Additional assessments of baseline medication adherence, physical activity (International Physical Activity Questionnaire: IPAQ),^41 42^ Cardiovascular disease (CVD)-specific health status (Seattle Angina Questionnaire: SAQ),^43^ health status (EuroQol five-dimensional questionnaire: EQ-5D)^44^ and smoking status were also conducted in person. Lastly, blood and urine samples were collected for local lab tests and eventual transfer to the core lab in Beijing at the biobank of NCCD. To ensure the standardisation and accuracy of the sample analysis results, we developed standard operating procedures and trained local study researchers repeatedly regarding samples collection, separation, storage and transfer process. Blood tests, including low-density lipoprotein cholesterol (LDL-C), glycaemic haemoglobin (HbA_1C_) and fasting blood glucose (FBG) will be analysed at the central laboratory. Research staff would collect the above information again as listed in table 4 at the follow-up visit. We conducted on-site monitoring of recruitment, physical measurements, sample collection and document completeness (eg, informed consent) by trained staff from NCCD to ensure the quality of data collection.

**Table 4 T4:** Baseline and follow-up data collection

Information	Baseline	6 months
Basic and contact information	√	√
Physical examination: BP, HR, waist circumference, weight, height	√	√
Ambulatory blood pressure	**√**	√
Outcome (death, myocardial infarction, angina, stroke, revascularisation, etc)	**√**	**√**
Hospitalisations	√	√
Current medications	√	√
Medication adherence	√	√
Physical activity (International Physical Activity Questionnaire)	√	√
CVD functional status (Seattle Angina Questionnaire)	√	√
Health status (EuroQol five-dimensional questionnaire)	√	√
Socioeconomic status	√	√
Risk factors control	√	√
Urine cotinine/nicotine test	√	√
Blood and urine samples for core lab and local test	√	√

BP, blood pressure; CVD, cardiovascular disease; HR, heart rate.

### Data management

A proprietary software platform was developed by the study Information Technology (IT) team for use in sending text messages to participants. The platform is capable of sending tailored and semipersonalised text messages to participants and also recording responses. Additionally, this web-based platform is used to monitor project progress, as well as provide management support for hospitals, staff members, equipment and sampling collection and transfer. Trained medical staff members fill out predesigned onscreen case report forms at each site, and data are then securely transmitted to the central server through automatic electronic transfer. To ensure the reliability and validity of the data, continuous checks are run to ensure that data being entered are complete and meet predefined data formats and ranges. The database is regularly backed up and password protected so that only a limited number of approved staff members can access the data. In order to ensure the confidentiality of all personal information, data confidentiality policies of NCCD on data collection, storage and analysis have been strictly imposed.

### Outcomes

In the CHAT Study, the primary outcome is the change in systolic blood pressure (SBP) after 6 months. Secondary outcomes include a change in proportion of patients achieving a SBP <140 mm Hg, change in proportion of non-smokers, change in medication adherence, as well as change in plasma mean level of LDL-C, change in level of body mass index (BMI) and change in level of physical activity. Exploratory outcomes include the prognosis of the patients at 6 months, such as death, non-fatal myocardial infarction, stroke and any rehospitalisation, as well as health status measured by SAQ and EQ-5D.

In the CHAT-DM Study, the primary outcome is the change in glycaemic HbA_1C_ as measured by the central blood sample. Secondary outcomes include a change in proportion of patients achieving HbA_1C_<7%, change in medication adherence, as well as change in mean level of FBG, SBP, LDL-C, BMI and physical activity. Exploratory outcomes include prognosis of patients at 6 months, including death, non-fatal myocardial infarction, stroke and any rehospitalisation, as well as health status (SAQ and EQ-5D).

Blood pressure is measured on the right upper arm after 5 min of rest in a seated position using an electronic blood pressure monitor (Omron HEM-7111; Omron Corporation, Dalian, China). Two measurements are taken and the mean value is calculated. If the difference between the two SBP or diastolic blood pressure readings is larger than 5 mm Hg, a third measurement is done, and the mean value of the three readings is calculated.^45 46^ HbA_1C_ is determined using a high-performance liquid chromatography technique with ADAMS A_1C_HA-8180 (ARKRAY, Japan). BMI is calculated by dividing weight in kilograms by height in metres squared. Physical activity is measured in metabolic equivalents of task per minute per week, using the short version of IPAQ.^41 42^ Smoking status is determined using either self-reported smoking status or urine-cotinine testing strip with a cut-off of 200 ng/mL cotinine (COT Cotinine Test Colloidal Gold; Hangzhou Clongene Biotech, China).^47 48^ Quality of life is measured using the short version of SAQ^43^ and EQ-5D.^44^ Local study staff obtained information of baseline hospitalisation, readmissions to hospitals and death during the patient’s interview, with medical records, death certificates or death records collected as supporting documents. If the patient died at home without any evidentiary material, a structured summary of death conversation with family members would be reported. All information was sent to NCCD for central adjudication according to prespecified criteria by trained clinicians. If the patient was rehospitalised in other hospitals, for example, the study investigators will contact the specific hospital, copy those medical records and transmit them to NCCD as required.

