**Methods and analysis:**

The Cardiovascular Health And Text Messaging (CHAT) Study and the CHAT-Diabetes Mellitus (CHAT-DM) Study are multicentre, single-blind, randomised controlled trials of text messaging versus standard treatment with 6 months of follow-up conducted in 37 hospitals throughout 17 provinces in China. The intervention group receives six text messages per week which target blood pressure control, medication adherence, physical activity, smoking cessation (when appropriate), glucose monitoring and lifestyle recommendations including diet (in CHAT-DM). The text messages were developed based on behavioural change techniques, using models such as the information-motivation-behavioural skills model, goal setting and provision of social support. A total sample size of 800 patients would be adequate for CHAT Study and sample size of 500 patients would be adequate for the CHAT-DM Study. In CHAT, the primary outcome is the change in systolic blood pressure (SBP) at 6 months. Secondary outcomes include a change in proportion of patients achieving a SBP <140 mm Hg, low-density lipoprotein cholesterol (LDL-C), physical activity, medication adherence, body mass index (BMI) and smoking cessation. In CHAT-DM, the primary outcome is the change in glycaemic haemoglobin (HbA_1C_) at 6 months. Secondary outcomes include a change in the proportion of patients achieving HbA_1C_<7%, fasting blood glucose, SBP, LDL-C, BMI, physical activity and medication adherence.

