### Randomisation and blinding

Participants were randomly allocated to either the intervention or the control arms in a 1:1 ratio using a computerised randomisation system. In order to achieve a balance of participants’ characteristics in both arms, we employed a stratified randomisation approach, based on age, gender, AMI history, education degree and medical insurance type within each study. Researchers, statisticians and clinic staff were blinded to treatment allocation.

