### Trial intervention

Participants in the intervention groups of the CHAT and CHAT-DM studies receive text messages about CHD risk factor modification for 6 months as well as standard treatment (described below). The control group in both studies receive two thank you text messages without risk factor modification support each month as well as standard treatment. A training session was held by research staff on enrolment to ensure that all participants were capable of receiving, reading and sending text messages on their mobile phones. Prior to commencement, a test message was sent to each participant to confirm the phone number and that the system was working effectively. Whether the test messages had reached the patients would be recorded by local study staff, and if patients did not receive messages, local study staff would confirm and update the correct phone number. Participants were also informed that they could withdraw from the study by responding to a text message with a specific character. Researchers at NCCD could monitor the status of text message delivery, review responses sent by participants and manage withdrawal via a customised software platform. For instance, logs were kept to assess the proportion of text messages successfully delivered, the exact time of messages being sent and the reasons for those that failed to be sent.

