**Medication adherence (1x/week)** Do you have a problem remembering to take your blood pressure medications? If so, try to tell your family about your medicine schedule so they can remind you.	**Medication adherence (1x/week)** Talk to doctors about your concerns and any uncomfortable symptoms after taking pills. Let your doctor help you to find the right medication for you.
**Physical activity (1x/week)** You can still choose low-intensity exercise even after heart attack, such as walking and t’ai chi, at a slower pace and stick to your exercise plan. Always consult your physician before beginning any exercise programme.	**Physical activity (1x/week)** Try brisk walking—a convenient, safe and cost-effective way of exercising! It’s good for your heart and will help control blood glucose.
**Smoking cessation (1x/week)**† Do you worry about your family having health problems because of your smoking? Quitting is an important choice you can make to benefit your family’s health, too. Secondhand smoke can cause respiratory disease, lung cancer and heart disease.	**Diabetes management (1x/week)** See a doctor before you travel. Always carry your diabetes medications and insulin, glucose meter and strips, so that you can better monitor your glucose. Carry some hard candy and crackers to avoid low sugar.
	**Lifestyle intervention (1×/week)** Individuals with diabetes should consume a balanced diet, and eat smaller but more frequent meals. Consider splitting your meal and save it for a snack later. Some healthy snack choices include tomatoes, cucumbers and sugar-free biscuits.

*In CHAT, non-smokers receive two general education messages per week, while smokers only receive one per week.

†In CHAT, only smokers receive smoking cessation messages.

CHAT, Cardiovascular Health And Text Messaging; CVD, cardiovascular disease; DM, diabetes mellitus.

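### CHAT's smoking outcome rests on self-report or cotinine with no rule for disagreement, and on one natural reading it is open to arm-dependent under-reporting

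*Protocol article*

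**What the plan says.** The Outcomes section of the protocol article gives the rule: "Smoking status is determined using either self-reported smoking status or urine-cotinine testing strip with a cut-off of 200 ng/mL cotinine". It gives no order of precedence between the two sources. Table 4 schedules the "Urine cotinine/nicotine test" at baseline and at 6 months.

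The same section lists the CHAT secondary outcome as "change in proportion of non-smokers" and states no denominator. The abstract ends its list of CHAT secondary outcomes with "physical activity, medication adherence, body mass index (BMI) and smoking cessation". No smoking outcome is listed for CHAT-DM.

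On who knows the allocation, the section on randomisation and blinding says: "Researchers, statisticians and clinic staff were blinded to treatment allocation". Participants are not on that list. On what they are sent, the footnote to Table 3 says: "In CHAT, only smokers receive smoking cessation messages". Controls receive "two thank you text messages without risk factor modification support each month".

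**The concern.** The article states the instrument, the device and the cut-off, but its rule does not classify a patient whose two results conflict. For blood pressure, the same section does settle disagreement: a third reading is taken if the first two differ by more than 5 mm Hg.

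The conflict that matters is a denial with a positive strip. An intervention-arm smoker is urged every week to quit and then asked by the trial whether he or she still smokes. A control smoker gets no such message. The urge to deny may therefore differ by arm. Blinded staff do not remove this, because the patient is the reporter. The Discussion concedes social desirability bias for medication adherence and physical activity and expects it to balance across arms. It does not mention smoking, although an objective test for smoking is scheduled at both visits.

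The two names for the outcome add a second gap. Cessation is a quantity among baseline smokers. A proportion of non-smokers, under intention to treat, is most naturally taken over everyone, including patients who had nothing to quit.

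**Working it through.** The documents give no figure for the smoking outcome, so there is none to reproduce. The smoking shares, quit rates and denial rates below are assumptions.

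**Step 1: what the wording allows.** For a patient who denies smoking and tests positive:
- if a denial is enough, the patient is a non-smoker;
- if a positive on either source makes a smoker, the patient is a smoker;
- if whichever source is at hand is used, the answer depends on which one that is.

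Only the second reading protects against false denial, to the extent that the strip catches it.

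**Step 2: false benefit under the first reading.** Let q be the true quit rate among baseline smokers, m the share of continuing smokers who falsely deny, and s the share of patients who smoke at baseline.

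Observed quit rate = q + (1 − q) × m. Difference over all patients = s × difference among smokers.

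Assume q = 20% in both arms, with m = 5% (control) and 15% (intervention):
- control: 0.20 + 0.80 × 0.05 = 0.24
- intervention: 0.20 + 0.80 × 0.15 = 0.32
- difference among smokers: 8 points, with no true effect
- over all patients at s = 20%, 30%, 40%: 1.6, 2.4, 3.2 points

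**Step 3: how often that would look significant.** Take q = 30%, no true effect, and extra denial in the intervention arm only. Patients analysed: 800 × 0.8 / 2 = 320 per arm, using the planned sample size and the 20% dropout allowance. The test is two-sided at 0.05; the chances count the favourable tail, which is 2.5% without bias. Ranges run over s = 15% to 45%.

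| Extra denial | Among smokers (points) | All patients (points) | Chance of false significance, all patients unadjusted | Same, smokers only |
|---|---|---|---|---|
| 5% | 0.70 × 5 = 3.5 | 0.5–1.6 | 4–6% | 6–9% |
| 10% | 0.70 × 10 = 7 | 1.1–3.2 | 7–14% | 11–24% |
| 20% | 0.70 × 20 = 14 | 2.1–6.3 | 15–42% | 29–69% |

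The last column shows that restricting the analysis to smokers without first repairing the classification makes a false benefit easier to detect.

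**Step 4: dilution of a true effect.** Assume true quitting of 30% versus 45% (15 points), 320 per arm, and no baseline non-smoker starting to smoke. The adjusted column comes from 4000 simulated trials per row; the other two power columns come from the formula for two proportions.

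| Baseline smokers | Effect in all patients (points) | Power, all, unadjusted | Power, all, adjusted for baseline smoking | Power, smokers only |
|---|---|---|---|---|
| 15% | 0.15 × 15 = 2.25 | 16% | 33% | 33% |
| 25% | 3.75 | 26% | 51% | 50% |
| 35% | 5.25 | 36% | 65% | 64% |
| 45% | 6.75 | 48% | 76% | 75% |

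The absolute difference shrinks by the factor s, for a true and a false effect alike. Adjusting for baseline smoking recovers nearly all the lost power.

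**The case against.** The strongest reply is that the sentence is short and fits a sound rule. If a positive on either source makes a smoker, a non-smoker is someone who denies smoking and tests negative, which is exactly the definition proposed below. A reader might infer that the trial has adopted a self-report endpoint. The document does not say so, and that inference fails.

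A second reply is that this is a condensed article whose analysis plan is not shown, and that discordant and missing strips are commonly settled there. This would answer a complaint of mere silence. It does not fully answer this one, because the article prints a classification rule and that rule, as worded, permits self-report alone.

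Third, a reader might infer that the analysis is fixed on all patients and is insensitive to quitting. That is not supported either. The denominator is not written, and the abstract's name points to smokers. The Statistical analysis section plans covariance analysis on baseline values where appropriate, and subgroup analyses by smoking status. Baseline non-smokers can also start or relapse, which an all-patient proportion captures and a smokers-only analysis drops. What stands is that the two names describe different quantities, and that baseline adjustment is not firmly committed for this outcome.

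Finally, only participants are left off the list of those blinded; clinic staff are on it. It would also be too strong to say that self-report alone is never needed, since a scheduled strip may still be missing.

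**Conclusion.** The point holds as a badly fixed outcome definition, not as a demonstrated bias. The printed rule leaves a denial with a positive strip unclassified, and one natural reading counts that patient as a non-smoker. Under that reading, modest differences in denial between arms produce a false benefit: 8 points among smokers in the Step 2 illustration, and 3.5 to 14 points across the Step 3 range. Under the stricter reading, denial caught by the strip produces none.

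The second part is the unresolved denominator. It costs substantial power only if the analysis covers all patients and is unadjusted.

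The scope is one CHAT secondary outcome. The primary outcome, the sample size and the CHAT-DM outcomes are untouched. The change is worth making because the messages target this outcome directly and the objective test is already scheduled.

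**What to change.** Before the 6-month data are analysed:
- Define a non-smoker, at baseline and at 6 months, as a patient who reports not smoking and has cotinine below 200 ng/mL. Count discordant patients as smokers.
- State how missing strips are handled, identically in both arms.
- Use one name and one denominator throughout: either cessation among baseline smokers (by the same rule), or the proportion of non-smokers in all patients with adjustment for baseline smoking.
- Report self-report alone as a sensitivity analysis.

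The cost is a few sentences in the outcome definition and no new measurement. The downside is that users of nicotine replacement may test positive; they should be flagged.

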### Statistical analysis

Intervention evaluation will be carried out on an intention-to-treat basis. Values of analysed parameters at baseline between intervention group and control group will be compared using Student’s t-tests for continuous variables or χ^2^ tests for categorical variables according to the analysis plan. Mann-Whitney U tests will be used where continuous data are not normally distributed. The primary analysis will employ analysis of covariance with baseline values of the analysed end points used as covariates when appropriate. The mean change of each risk factor will also be compared between groups. In all analyses, 95% CIs and two-sided P values will be reported. We will conduct a prespecified second analysis with adjustment for patient characteristics as well as subgroup analyses based on age, sex, education, smoking status and tertile levels of end points.

All sample size calculations in both studies are for 80% power and 0.05 (one-sided) level of significance, allowing for 20% dropout rate during follow-up. In the CHAT Study, we estimate a mean SBP level of 132 mm Hg (SD, 18 mm Hg) in the study population according to the report of previous studies,^49^ and assume an absolute difference in SBP changes of 5 mm Hg at 6 months from baseline in the intervention group and no change in the control group. A total sample size of 800 patients would be adequate to detect this difference in SBP changes between two groups even when considering the potential non-compliance to the intervention. In the CHAT-DM Study, we assume a mean HbA_1C_ level of 7.2% (SD, 1.6%) based on data from studies involving similar populations^50 51^ and supposed a 0.5% absolute difference in HbA_1C_ changes in treatment group and no change in the control group at 6 months from the baseline. A total sample size of 500 patients is adequate to detect this difference in HbA_1C_ change between two groups even when considering the potential non-compliance to the intervention. The trial results will be reported in accordance with the Standard Protocol Items: Recommendations for Interventional Trials (SPIRIT) checklists.

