## Methods and analysis

### Study overview

The CHAT and CHAT-DM studies are multicentre, single-blind, two-arm, randomised controlled trials of an automated mobile phone text message-based intervention with 6 months of follow-up. Patients were recruited from 37 hospitals across 17 provinces in China (figure 1, online supplementary material 1). The enrolment of participants began on 16 August 2016. The two studies were registered at http://www.clinicaltrials.gov (NCT02888769 and NCT02883842) accordingly. We retrospectively registered the trial 7 days later after enrolment of the first patient in CHAT Study, beyond the International Committee of Medical Journal Editors (ICMJE) recommendations of the journal, as we referred to the Food and Drug Administration (FDA) AA801 public law on the Clinicaltrials.gov website that clinical trials are registered no later than 21 days after the first patient was enrolled. The recruitment was completed in April 2017, and the last follow-up visit is expected to finish in October 2017. All participants provided written informed consent at the initial trial visit.

10.1136/bmjopen-2017-018302.supp1Supplementary file 1

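### The primary ANCOVA omits the five stratification factors and makes the baseline covariate conditional: a modest loss of precision in the conservative direction

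*Protocol article*

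**What the plan says.** On allocation, the section Randomisation and blinding of the protocol article states: "Participants were randomly allocated to either the intervention or the control arms in a 1:1 ratio using a computerised randomisation system". It adds: "we employed a stratified randomisation approach, based on age, gender, AMI history, education degree and medical insurance type within each study". Hospital is not in that list, although the Study overview says: "Patients were recruited from 37 hospitals across 17 provinces in China".

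On the primary model, the Statistical analysis section states: "The primary analysis will employ analysis of covariance with baseline values of the analysed end points used as covariates when appropriate". No rule says when the closing qualifier applies. The section then assigns further adjustment elsewhere: "We will conduct a prespecified second analysis with adjustment for patient characteristics". On reporting it says: "In all analyses, 95% CIs and two-sided P values will be reported".

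**The concern.** The article names one covariate for the primary analysis and puts other adjustment outside that analysis. Read as written, the five factors that shaped the allocation are absent from the primary model.

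Stratification balances these factors between the arms, so the treatment estimate varies less than under simple randomisation. A model that ignores the factors leaves the variance they explain in the residual, so it does not credit that gain. The reported standard error is then larger than the true one. The stake is precision: a wider interval and a larger P value than the design has earned.

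The qualifier on the baseline value is a second, smaller weakness. Blood pressure and blood samples are both scheduled at baseline (Data collection and its table of baseline and follow-up data). For change in SBP and change in HbA1c, the condition therefore serves no purpose and leaves the primary model less than fully fixed.

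**Working it through.** **Inputs from the Statistical analysis section.** CHAT: SD 18 mm Hg, difference 5 mm Hg, N = 800. CHAT-DM: SD 1.6%, difference 0.5%, N = 500. Both: 80% power, one-sided 0.05, 20% dropout. Non-compliance is mentioned without a figure.

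**Assumption.** R² is the share of the residual variance, after baseline, that the five factors explain. The article gives no value. I use 0.02 to 0.15.

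**Step 1. The plan's own sample sizes.** n per arm = 2(z_α + z_β)²SD²/d², and the total is divided by 0.8.

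| Trial | One-sided 0.05 | Two-sided 0.05 | Stated |
|---|---|---|---|
| CHAT | 161 per arm, 403 in total | 204 per arm, 510 in total | 800 |
| CHAT-DM | 127 per arm, 318 in total | 161 per arm, 403 in total | 500 |

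The stated totals are not the direct output of this formula, but they exceed it. The claim that they are adequate is not contradicted.

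**Step 2. Effect on the standard error and the test.** With fully balanced strata, model SE / true SE = 1/√(1 − R²), and the true two-sided size of the baseline-only test is 2[1 − Φ(1.960/√(1 − R²))].

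| R² | SE too large by | True size |
|---|---|---|
| 0.02 | 1.0% | 0.048 |
| 0.05 | 2.6% | 0.044 |
| 0.10 | 5.4% | 0.039 |
| 0.15 | 8.5% | 0.034 |

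**Step 3. Power, two-sided 0.05, full compliance.** The stated SD serves as the residual SD, so no credit is taken for baseline. Completers per arm are 320 (CHAT) and 200 (CHAT-DM).

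- CHAT-DM: SE = 1.6√(2/200) = 0.160; 0.5/0.160 = 3.125; power = Φ(3.125 − 1.960) = 87.8%. Multiplying the SE by √(1 − R²) gives 88.4%, 89.4%, 90.9% and 92.4% at the four values of R².
- CHAT: SE = 18√(2/320) = 1.423; 5/1.423 = 3.514; power = Φ(3.514 − 1.960) = 94.0%. With the factors: 94.4%, 95.0%, 95.9% and 96.8%.

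These gains are upper limits, for two reasons.

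- With full stratum balance the baseline-only estimate is itself less variable. At R² = 0.15 the baseline-only test then has power Φ((3.125 − 1.960)/0.922) = 89.7% in CHAT-DM and Φ((3.514 − 1.960)/0.922) = 95.4% in CHAT. The gains shrink to about 2.7 and 1.4 points.
- If baseline correlates 0.5 with the outcome (assumed), the baseline-only ANCOVA already has 95.0% power in CHAT-DM and 98.2% in CHAT.

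**Step 4. Simulation of the stratification factors.** Settings: 640 completers, five two-level factors, permuted blocks of 4 within strata, baseline correlation 0.5, 3,000 runs per setting.

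- R² = 0.15: the baseline-only model reports SE 0.0685 against a true SD of 0.0627 and rejects 3.2% of the time. With the factors added, SE is 0.0632 against 0.0626, and rejection is 4.7%.
- R² = 0.05: the model SE falls from 0.0685 to 0.0667. Rejection is 5.2% without the factors and 5.7% with them. The Monte Carlo error is √(0.05 × 0.95/3000) = 0.4 points, so the simulation cannot resolve so small an effect.

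**Step 5. Simulation of hospital, not stratified.** With 15% of the residual variance between hospitals, the baseline-only SE is 0.0684 against a true SD of 0.0690, and rejection is 5.3%. The SE is right. Adding 36 hospital indicators lowers the SE to 0.0650 at that share, gives nothing at a 5% share (0.0688 against 0.0685), and costs precision at zero (0.0705 against 0.0685). A random intercept was not simulated.

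**Step 6. Size of the baseline condition.** Leaving baseline out multiplies the SE by 1/√(1 − ρ²): 1.05, 1.15 and 1.40 at ρ = 0.3, 0.5 and 0.7 (ρ assumed).

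**The case against.** The best defence is that the error is safe. The estimate is unbiased, the type I error rate does not exceed its nominal level, and the cost may be close to nothing if the factors add little once baseline is known. At R² = 0.02 the SE changes by 1%. That stands, and it limits the weight of the point.

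A second defence is that covariate lists belong in the analysis plan, which the article mentions and which is not shown. The unnamed characteristics in the second analysis are indeed no finding. But the article does more than stay silent: it says what the primary model adjusts for and places other adjustment outside it. A better secondary analysis does not repair the primary interval and P value.

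A third is that the qualifier on baseline may only exempt endpoints without a baseline value, such as death. That is a fair reading, and it supports stating plainly that the exemption does not cover either primary outcome.

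Three stronger readings are tempting but are not supported:

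- A reader might infer that ignoring the 37 hospitals makes the SE wrong. Patients are randomised individually and hospital is not a listed stratum, so its omission costs at most some precision.
- A reader might infer that CHAT-DM becomes underpowered. That needs a non-compliance rate, which the article does not give, and no credit for baseline adjustment.
- A reader might infer that the planned baseline significance tests choose the covariates. Nothing in the text links them, and statisticians are said to be blinded to allocation.

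**Conclusion.** The point holds in a modest form. As written, the primary model does not reflect the stratified allocation, and its baseline term is conditional without need. To the extent that the five factors predict the outcome beyond baseline, the primary analysis is conservative. Over the assumed R² range of 0.02 to 0.15, the SE is about 1% to 8.5% too large. The power recovered is at most about 5 points in CHAT-DM and 3 points in CHAT, and less with full stratum balance or a useful baseline correlation.

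The SE and size figures assume full balance within strata. The article gives neither the number of levels per factor nor the allocation algorithm, and with sparse cells the balance may be partial. The baseline-only SE would then be less overstated, while adjustment would still recover precision. The validity of the trials is not in question.

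**What to change.** In the analysis section, or in the analysis plan before unblinding, fix the primary model for each trial as the 6-month value regressed on treatment, the baseline value of the endpoint (always included) and main effects of the five stratification factors. Main effects suffice, because fully crossed cells could be very sparse. Restrict the qualifier on baseline to endpoints that have no baseline value. Keep the baseline-only ANCOVA as a sensitivity analysis. A random intercept for hospital may be added for precision, but validity does not require it.

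The cost is a change of wording. The stratification factors had to be recorded in order to randomise, and the baseline endpoint values are already scheduled, so no new data are needed. By the article's dates follow-up was still running, with the last visits expected in October 2017.
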